# A cluster randomised controlled trial, process and economic evaluation of two large-scale quality improvement interventions embedded with a national clinical audit to improve the care for young adults with type 2 diabetes (EQUIPD2): study protocol

**DOI:** 10.1186/s13012-025-01479-8

**Published:** 2026-01-06

**Keywords:** Audit and feedback, Quality improvement, Diabetes, Randomised controlled trial, Learning health system

## Abstract

**Background:**

Young adults (18–39 years) with type 2 diabetes have an increased loss of life expectancy and a greater risk of complications such as retinopathy, sexual health problems and foot disease than people diagnosed with type 2 diabetes later in life. Globally, there are increasing numbers of young adults with type 2 diabetes. Evidence describes both care (for example, prescribing) and improvement practices (for example, case management) that improve outcomes for people with type 2 diabetes.

The National Diabetes Audit (NDA) provides feedback describing variation in both care and outcomes in young adults. Feedback facilitation can increase the effectiveness of audit feedback. Working collaboratively between researchers, audit providers, patients, clinicians and policy-makers, we have developed two feedback facilitation interventions deliverable at scale across England. We will evaluate whether theory-informed virtual educational materials with email support (low-intensity intervention) and / or virtual workshops (medium-intensity intervention) improve outcomes for young adults with type 2 diabetes.

**Methods:**

An efficient, pragmatic cluster randomised controlled trial using routine data with a theory-informed process and economic evaluation. The interventions will be delivered alongside the NDA to primary care networks (small groups of general practices) across England. Our primary outcome will be HbA1c level at 16-months post-randomisation in young adults with type 2 diabetes and baseline HbA1c ≥ 58 mmol/mol. Secondary outcomes assess the proportion with an HbA1c below recommended thresholds, prescription consistent with recommendations and delivery of recommended care processes. We will investigate impacts on equity. We will explore implementation, engagement and fidelity through interviews, observations, documentary analysis and surveys. An economic evaluation will estimate cost-effectiveness and budget impact.

**Discussion:**

Our study embeds a further evaluation within the NDA, strengthening its role as a national diabetes learning health system. Our findings will have implications for intervention providers and funders seeking improvement in care and outcomes, and for our understanding of large-scale implementation strategies.

**Trial registration:**

ISRCTN 52205353 Registered 12 March 2025. https://www.isrctn.com/ISRCTN52205353.

**Supplementary Information:**

The online version contains supplementary material available at 10.1186/s13012-025-01479-8.

Contributions to the literature
Feedback facilitation can increase the effectiveness of audit and feedback.It is not known whether or how to deliver feedback facilitation at scale.We will evaluate the effect of two feedback facilitation interventions delivered to primary care networks across England on the achievement of recommended glucose levels. We will investigate impact on equity and cost-effectiveness, and explore implementation and engagement with the interventions.Our study embeds a further evaluation within the NDA, strengthening its role as a national diabetes learning health system and generating learning for implementation scientists, intervention providers and funders.

## Background

Early onset type 2 diabetes, defined as before age 40 years, differs from later onset and is associated with greater risk of complications and reduced life expectancy [1]. Over 145,000 young adults (18–39 years) in England have type 2 diabetes.

The global prevalence of early onset diabetes is increasing [2]. In England, type 2 diabetes is now more common in people under 40 than type 1 diabetes and disproportionately affects people from minority ethnic groups and young adults living in deprived areas. For example, 35% of young adults with type 2 diabetes are from the most deprived quintile, which is considerably higher than the 22% of 60–79 year olds in the same quintile. Prevalence of type 2 diabetes in young adults is almost fourfold higher among Asian people and over twofold higher among Black people relative to people of white ethnicity [1].

The English National Institute for Health and Care Excellence (NICE) recommends clinicians tailor treatment according to individualised patient goals and medication use. An HbA1c below 48 mmol/mol is recommended for many people with type 2 diabetes [3]. Where HbA1c is 58 mmol/mol or higher, NICE specifies additional care: reinforcement of advice about diet, lifestyle, adherence to drug treatment and more intensive drug treatment. In England, over 60,000 adults under 40 years have HbA1c levels ≥ 58 mmol/mol [3] putting them at greater risk of retinopathy, nephropathy, neuropathy, cardiovascular disease, sexual health problems and foot disease [1]. These young adults living with type 2 diabetes face challenges engaging with care, such as greater stigma, work or family commitments, or moving area for education [2]. They are also less likely to receive recommended diabetes care processes such as foot checks, blood pressure and cholesterol monitoring or annual clinical reviews to help reduce risk of complications [1, 4]. Addressing modifiable factors in healthcare such as ways of working, staff skills, knowledge, attitudes and beliefs may support young adults to engage with and respond to care [5]. NHS England (NHSE) has identified care for this patient group as an improvement priority [6].

A range of programmes exist to improve care and outcomes for people with diabetes. Amongst these, the National Diabetes Audit (NDA) aims to drive improvements in care and outcomes. The NDA is a registry, and feedback provider, integrating patient-level primary and secondary care records on people diagnosed with diabetes, with near-universal coverage. Funded by NHSE, the NDA is one of around 60 national audits in England [7]. The NDA provides feedback on recommended processes of care (e.g. number and proportion of people who have their blood glucose levels checked) and attainment of treatment goals (e.g. glucose control) to general practices and primary care networks (PCNs). PCNs are small groups of general practices, typically located close to each other, working together to coordinate care delivery. The median number of young adults with type 2 diabetes and HbA1c above or equal to 58 mmol/mol is 56 (inter-quartile range 3 to 89 young adults). Feedback highlights areas for improvement to stimulate change. Systematic review evidence indicates that audit and feedback modestly improve care delivery [8]. However, adding feedback facilitation as a co-intervention may result in greater improvement [9, 10].

We have developed two feedback facilitation interventions suitable for delivery at scale within the NDA to all PCNs in England: medium-intensity feedback facilitation involving virtual workshops; and low-intensity feedback facilitation delivered through virtual educational materials and email.

Whilst NHSE has agreed to fund the medium-intensity co-intervention, it is unknown whether it is effective or cost-effective and whether such intensity is needed [11]. Embedding the research within the NDA provides resources for delivery, closely reflects usual delivery of such interventions and supports PCN engagement. It also ensures a direct route for implementation of research findings by the NDA as well as offering transferable evidence for other national audits.

We will evaluate the effectiveness of NDA feedback with (i) medium-intensity facilitation to PCNs and (ii) low-intensity facilitation to PCNs compared to NDA feedback alone in reducing the HbA1c of young adults with type 2 diabetes and HbA1c ≥ 58 mmol/mol. We will explore facilitation implementation, engagement, fidelity and tailoring of actions and estimate the cost-effectiveness of medium- and low-intensity facilitation.

## Methods

### Study design

An efficient 3-arm cluster randomised trial using routine NDA data with parallel process and economic evaluations. The facilitation interventions will target PCNs to help them achieve blood glucose goals in young adults with type 2 diabetes. The intervention programme theory and content is described below, and in an adapted Template for Intervention Description and Replication (TIDieR) [12] (Appendix A) and a logic model (Appendix B). The interventions draw upon organisational readiness for change [13] and Normalisation Process Theory [14], supporting participants to commit to change, select tailored improvement actions guided by an informational assessment and to reflexively monitor their collective action. The logic model describes consistency with Clinical Performance Feedback Intervention Theory (CP-FIT) [9].

### Study setting

PCNs in England.

### Cluster eligibility

All PCNs in England.

### Patient eligibility

All young adults (18–39 years) living with type 2 diabetes and an HbA1c level above or equal to 58 mmol/mol in England in the previous year, identified through the national audit before the intervention period (baseline).

### Randomisation

All PCNs will be randomised to one of three study arms: (i) medium-intensity facilitation with NDA feedback, (ii) low-intensity facilitation with NDA feedback, or (iii) NDA feedback alone (waitlist control group) on a 1:1:1 basis, using a computer-generated minimisation programme within the Clinical Trials Unit (Fig. 1).

**Fig. 1 Fig1:**
[figure not shown]
CONSORT flow chart

### Minimisation factors

We will stratify by PCN-level baseline proportion of young adults with type 2 diabetes who have an HbA1c ≥ 58 mmol/mol (above or below median) and by NHS Integrated Care Board (ICB; NHS organisations responsible for planning and commissioning health services for their local populations). ICBs vary by the number of PCNs (median 27; IQR 19 to 42) and number of young adults with type 2 diabetes and raised HbA1c above 58 mmol/mol (median 1732; IQR 1250 to 2498). Stratifying by ICB will help to minimise any imbalances in patient characteristics including age, sex, ethnicity and deprivation, but we will also account for these patient-level characteristics in the statistical and economic analyses.

### Blinding

Allocation concealment is not feasible in this trial.

### Intervention

Both feedback facilitation co-interventions will be delivered by Diabetes UK (a charity that aims to reduce harm from diabetes) on behalf of the NDA. Both co-interventions support the implementation of care practices by primary care staff and patients to achieve NICE-recommended blood glucose targets. The logic model (see Appendix B) represents the programme theory of how we hypothesise these interventions will produce their outcomes. Intervention development involved patient, public, policy-maker and clinician prioritisation of young adults with type 2 diabetes as the focus. The intervention content was created through a stakeholder workshop involving people with diabetes, policy-makers, clinicians, Diabetes UK employees and implementation scientists, and discussions with an advisory group constituted of people with diabetes. This included consideration of the evidence-based practices and how to implement these practices. It led to the incorporation of content from both young adults describing their experience of diabetes and care, and of vignettes from higher-performing primary care networks.

For both interventions, we propose that the identified evidence-based [15] improvement practices (case management; patient education; promotion of self-management; patient reminders; enhanced prescribing) will improve blood glucose. These evidence-based practices will be more likely to happen if clinical leaders within PCNs undertake collective actions that address local contexts (e.g. to change staff knowledge, beliefs, ways of working). These actions result from setting new behaviour and outcome goals, informed by an informational appraisal and supported by organisational commitment [13]. As shown in the logic model, behaviour change techniques (e.g. credible source, information on consequences [16]) have been linked within both interventions to both informational appraisal and change commitment. Ongoing review of NDA feedback supports participants’ reflexive monitoring of the collective actions taken to improve outcomes.

Intervention components draw on CP-FIT theory [9] hypotheses (e.g. perceived to support positive change rather than punish suboptimal performance; compare recipients’ current performance to that of other health professionals, organisations or regions; provide solutions to suboptimal performance or support recipients to do so).

The low- and medium-intensity feedback facilitation interventions include overlapping behaviour change techniques but differ in terms of resource implications for both healthcare deliverers and PCN recipients. Where content is only delivered in the medium-intensity feedback facilitation (e.g. group delivery of content), this is depicted in the logic model (Appendix B).

PCNs will be offered the interventions to which they have been allocated via an email distributed from Diabetes UK via NHSE regions and ICBs. Staff in PCNs allocated to the medium intensity intervention will be invited to participate in 7 virtual workshops. Staff in PCNs allocated to the low intensity intervention will be offered access to asynchronous web-based training with email support. For each intervention arm, the emails inviting participation will be signed by the clinical and improvement lead and detail that the support for improvement is free, delivered by DiabetesUK and provides learning from higher performing PCNs, learning from young adults, help to identify high-risk population and best practice guidance. The invite will also describe the reason for focussing on young adults with type 2 diabetes and how the learning may help different goals, including improved outcomes, increased efficiency of care, evidence of quality improvement activity and may increase practice income. It will detail the target audience and invite them to register via a virtual registration form.

Waitlist control will receive usual NDA feedback alone. After the trial follow-up period, the PCNs allocated to this group will also receive feedback facilitation. The design will be informed by early process evaluation findings; the NDA contract requires delivery before trial data analysis is possible.

### Outcomes

HbA1c level drawn from routine NDA data at 16-months post-randomisation in young adults with type 2 diabetes and baseline HbA1c ≥ 58 mmol/mol. We have chosen a 16-month follow-up period as it allows for a latent period for (i) PCNs and their member general practices to engage with facilitation, plan and initiate changes in clinical practice and (ii) for patients to consult, consider and start any new treatments or make any suggested lifestyle changes and for any benefits to be reflected in subsequent HbA1c measurements.

Secondary outcomes will comprise:Proportion with an HbA1c of < 58 mmol/mol.Proportion with an HbA1c of < 48 mmol/mol.Proportion prescribed both metformin and SGLT2 inhibitor.Proportion in whom the last blood pressure reading (measured in the preceding 12 months) is 140/80 mmHg or less (or equivalent home blood pressure reading).Proportion with statins prescribed.Proportion receiving NICE-recommended care processes in the preceding 12 months: blood pressure check; serum creatinine testing; urinary albumin: creatinine ratio testing; foot examination and risk classification; smoking status; retinal screening; body mass index; and referral to a structured education programme.

In young adults with baseline HbA1c ≥ 48 and < 58 measurement, we will examine the proportion with HbA1c ≥ 58 mmol/mol at follow-up to check for any unintended distributional consequences from focusing resources on those patients with higher HbA1c at baseline.

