### Data collection

Trial outcomes will be assessed using routinely collected individual patient data which is extracted from GP clinical systems by the NDA via the General Practice Extraction Service. We will use NDA-held demographic data in assessing effects on equity. The NDA validates, monitors and reports on data quality [4]; the NDA data quality report provides support that our selected measures are reliable.

The analysis will include outcome data from 12 months before randomisation to 16 months after randomisation.

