### Economic evaluation

An analysis plan will be written following Bristol Health Economics Analysis Plan (HEAP) guidance [25] and, as far as possible, the evaluation will align with the trial statistical analysis plan and adhere to the NICE reference case. All analyses will adopt the NHSE perspective and all cost and QALY measures will be discounted at the rate of 3.5% per annum. Our analysis will comprise three components:Within-trial economic evaluation and budget impact analyses.Design: An intention-to-treat, cost-effectiveness and cost-consequence analysis with a time horizon of 18 months and budget impact analysis using patient-level NDA data and intervention cost data.Data collection: Within-trial biomarker and resource use data collected through the NDA between baseline and 18 months post-randomisation will be used to assess health outcomes and healthcare costs. Healthcare cost data will include primary care prescriptions (glucose lowering drugs, antihypertensives and statins), inpatient (diagnosis, procedure, length of stay) and some outpatient data. The incremental costs of the two interventions when compared to NDA feedback alone will be assessed using a bottom-up, micro-costing approach [26]. This will draw on resource use data collected from people involved in facilitation delivery (e.g. NDA improvement lead, NDA administrator) as a fully integrated component within the interviews and surveys conducted as part of the process evaluation. These resources are likely to span intervention refinement, delivery and response activities; consumable costs incurred (e.g. printed material) and staff time (and grade) required; and additional activities that result from the intervention (e.g. meetings with stakeholders, local team training, additional consultations with patients).Analysis: The within-trial cost-effectiveness analysis will assess cost per unit change in HbA1c. The cost-consequence analysis will assess changes in all other NDA biomarker outcomes (e.g. cholesterol). Each resource use item, including staff time, will be costed using unit cost data available from routine sources, e.g. national healthcare databases such as Personal Social Services Research Unit (PSSRU) data [27, 28]. We will seek to capture the variance in costs that might occur across centres and incorporate this uncertainty in the analysis. We will also empirically estimate the denominator sample for deriving the per patient intervention cost. Given the high incidence and prevalence of type 2 diabetes in young adults, and thus potentially large ongoing costs to NHSE of delivering the intervention, an NHSE-wide budget impact assessment will also be conducted. Cost and outcome data will also be analysed for equity relevant subgroups as defined in the trial statistical analysis to inform the equity informative cost-effectiveness analysis (see below).Lifetime cost-utility analysis:Design: An intention-to-treat, cost-utility analysis with a time horizon of a lifetime, using intervention cost data, patient-level NDA data and the UK Prospective Diabetes Study Outcomes Model 2 (UKPDS-OM2) patient-level simulation model [29].Analysis: The patient-level demographic (e.g. age, ethnicity) and biomarker data collected during the within-trial period will be used as inputs to the UKPDS Outcomes Model v2.2 [29], which is a commercially available microsimulation model, pre-built, externally and internally validated, and recently updated by the University of Oxford to project long-term type 2 diabetes outcomes. The model will be used to estimate incremental lifetime healthcare costs and QALYs between the waitlist control and intervention groups by forecasting annually until death the progression of cardiovascular and type 2 diabetes complication risk factors (e.g. cholesterol, HbA1c, heart rate, smoking status, systolic blood pressure, weight, time since diabetes diagnosis) and the occurrence of eight events (e.g. myocardial infarction, ischaemic heart disease, stroke, amputation, blindness, renal failure). The primary outcome measure will be an incremental cost effectiveness ratio (ICER) assessing the aggregate-level incremental cost per QALY. We will also report net (monetary) benefit, which is a rearrangement of the ICER and estimated as: (λ x QALYs) – Costs, where λ is the willingness to pay threshold per health gain (in the case of NICE,

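### The one glucose-lowering prescribing outcome counts prevalence of a single drug pair: valid between arms, but on its own a weak test of enhanced prescribing

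*Protocol article*

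**What the plan says.** The Outcomes section lists two prescribing outcomes. One concerns glucose-lowering treatment: "Proportion prescribed both metformin and SGLT2 inhibitor". The other is "Proportion with statins prescribed". The first has no initiation or change component and no restriction by baseline treatment, and Patient eligibility excludes nobody by current drugs. The line gives no time window, so measurement at follow-up is inferred.

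Four other places bear on it:
- The abstract (Methods) describes the secondary outcomes as covering "prescription consistent with recommendations and delivery of recommended care processes".
- Background says that NICE "recommends clinicians tailor treatment according to individualised patient goals and medication use" and that, at 58 mmol/mol or higher, additional care is "reinforcement of advice about diet, lifestyle, adherence to drug treatment and more intensive drug treatment". No drug pair is named there.
- Intervention gives the practices expected to lower glucose as "case management; patient education; promotion of self-management; patient reminders; enhanced prescribing".
- On data, Data collection states: "The analysis will include outcome data from 12 months before randomisation to 16 months after randomisation". Economic evaluation obtains prescriptions of glucose-lowering drugs generally, for costing.

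Data analysis plans mixed effects logistic regression for binary outcomes. The covariates it names (age, sex, ethnicity, deprivation, stratification factors) are introduced as an open list and do not include the outcome's baseline value.

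**The concern.** Every patient in the main cohort has a baseline HbA1c of 58 mmol/mol or more, and the programme theory expects part of any benefit to come through changed prescribing. The listed outcome records who holds one regimen, not whose treatment changed. A patient already on both drugs counts as a success although nothing has been done. A patient not on the pair whose treatment is intensified with a different class, without completing the pair, counts as a failure.

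At stake is the interpretation of the mechanism, not the primary result. A null finding on the pair could be reported as no effect on prescribing when practices had intensified treatment in other ways. An HbA1c effect would then be hard to connect with the prescribing step in the logic model.

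**Working it through.** **The plan's own figure.** Inputs from Study procedure: 1150 PCNs, 41,365 patients, 10% loss, ICC 0.01, CV 1.62, SD 18.7, difference 2 mmol/mol, 2.5% per comparison (two-sided assumed).
- Analysed per arm: 41,365 × 0.9 / 3 = 12,409.5. Mean cluster size: 37,228.5 / 1150 = 32.37.
- Design effect: 1 + [(1.62² + 1) × 32.37 − 1] × 0.01 = 2.163. Effective n per arm: 12,409.5 / 2.163 ≈ 5736.
- SE = 18.7 × √(2/5736) = 0.349. Power = Φ(2/0.349 − 2.241) = 99.98%. The stated figure of more than 99% reproduces. No power is stated for the prescribing outcome.

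**Dilution by baseline users alone (assumed rates).** Let b be the share on the pair at baseline, all staying on it, and let new pair prescribing among the rest rise from 10% to 15%. The whole-cohort difference is (1 − b) × 5 points: 5.0, 4.5, 4.0, 3.5 and 3.0 at b = 0, 10, 20, 30 and 40%. Power on the same effective n is above 99.9% at b = 0 and 10%, then 99%, 95% and 84%. This part is mild.

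**Dilution plus additions outside the pair (assumed rates).** Let p0 be baseline pair use, with 90% of users retained. Let i be the share given any new glucose-lowering class, 30% in control and 35% with facilitation. Let s be the share of additions that complete the pair among patients not on it.
- Prevalence = 0.9·p0 + (1 − p0)·s·i
- SE = √[(pc·qc + pt·qt) × 2.163 / 12,409.5]; power = Φ(difference/SE − 2.241)
- Adjusting for baseline pair use: R² = 1 − W/V. V is the sum over arms of p(1 − p). W is the sum over arms of p0 × 0.9 × 0.1 + (1 − p0)·(s·i)(1 − s·i). The SE is multiplied by √(1 − R²), with the design effect unchanged.

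Example, p0 = 0.3 and s = 0.3: control 0.27 + 0.7 × 0.09 = 0.333; facilitated 0.27 + 0.7 × 0.105 = 0.3435; difference 0.0105; SE 0.00883; power Φ(1.189 − 2.241) = 15%. R² = 0.60, adjusted SE 0.00556, power 36%. Of control successes, 0.27/0.333 = 81% were already on the pair.

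| p0 | s | Control | Facilitated | Difference (points) | Power, unadjusted | R² | Power, adjusted |
|---|---|---|---|---|---|---|---|
| 10% | 30% | 17.1% | 18.45% | 1.35 | 36% | 0.40 | 58% |
| 30% | 30% | 33.3% | 34.35% | 1.05 | 15% | 0.60 | 36% |
| 10% | 60% | 25.2% | 27.9% | 2.7 | 85% | 0.23 | 93% |
| 30% | 60% | 39.6% | 41.7% | 2.1 | 52% | 0.43 | 79% |
| 10% | 80% | 30.6% | 34.2% | 3.6 | 97% | 0.17 | 99% |
| 30% | 80% | 43.8% | 46.6% | 2.8 | 78% | 0.35 | 93% |
| 10% | 100% | 36.0% | 40.5% | 4.5 | 99.7% | 0.13 | 99.9% |
| 30% | 100% | 48.0% | 51.5% | 3.5 | 93% | 0.28 | 99% |

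A new-class measure would show the assumed change from 30% to 35% directly: SE 0.00873, power 99.98%.

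**Sensitivity.** The ICC of 0.01 was set for HbA1c. At an assumed 0.03 the design effect is 4.49. Unadjusted power for s = 30-60% is then 8-51%, adjusted power is 18-64%, and the new-class measure has 96%. All of this is a difference-scale approximation to the planned logistic model.

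**The case against.** The strongest reply is that the outcome was never meant to measure intensification. The abstract presents it as concordance with recommendations, and a simple proportion is the ordinary form for that, as with statins. Someone stably on the regimen is concordant. That stands, and the outcome should stay.

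A reader might go further and infer that the trial cannot show whether prescribing was enhanced, or that any addition other than the pair scores as failure. The documents support neither. Randomisation should give similar baseline pair use across arms, so the comparison validly estimates the effect on pair prescribing; it is diluted and noisier, not biased. A patient already on the pair who adds a third drug remains a success, so the blind spot is confined to patients not on the pair.

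Three further replies have weight. Baseline adjustment of a secondary outcome may already be in the analysis plan, which is not shown, so its absence from the article is not an error. The process evaluation will look for the hypothesised mechanisms, and the costing draws on wider prescribing data, so change outside the pair need not go unseen; it simply has no listed effectiveness outcome. And the low power figures depend on assuming that only 30-60% of additions complete the pair, for which the documents give no basis either way.

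**Conclusion.** The point holds as a limited, inexpensive improvement. The sole glucose-lowering prescribing outcome is a sound between-arm concordance measure but a weak stand-alone test of the enhanced-prescribing mechanism. Baseline users by themselves cost little: power stays at about 84% or more with up to 40% on the pair, under the assumed rise from 10% to 15% among the rest. The larger loss comes when intensification runs through other classes, and that share is unknown. Baseline adjustment recovers some precision, but it cannot reveal additions outside the pair. Nothing here affects the primary outcome or its power.

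**What to change.** 1. Keep the pair outcome. State that its mixed effects logistic model adjusts for whether the patient was prescribed both drugs in the 12 months before randomisation. The resulting odds ratio is conditional on that status and should be described so.
2. Before the final analysis, pre-specify one supportive, drug-neutral secondary measure: any glucose-lowering class prescribed by month 16 that was not prescribed in the 12 months before randomisation.
3. State that a null result on the pair will not be read as no change in prescribing.

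Cost: wording in the outcome list and analysis plan, and derived variables from prescribing data already planned. One check is needed. Data collection takes outcome data back 12 months before randomisation, but Economic evaluation describes resource-use data from baseline onward, so confirm that the extract for all glucose-lowering classes covers the earlier year. The downsides are one more secondary outcome, and a measure that counts class switches as new prescribing and misses dose changes. It therefore supports the listed outcome and does not replace it. Which drugs should be used is a clinical matter and is not judged here.
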